### Conceptual framework for study design

The ALSTAR2 study design is based on the conceptual framework depicted in Fig. 3. As aging transitions to early AMD, our framework focuses on three factors - retinal structure, visual function, and genes – and three partly overlapping epochs in time. As depicted by the gray area in Fig. 3, the first longitudinal epoch in time addresses the aging process and the relationship between structure and RMDA, a measure of retinoid re-supply. The second epoch addresses the relationship between structure and scotopic sensitivity as aging transitions into early AMD. The third epoch addresses the transition from early to intermediate AMD and the relationship between mesopic acuity and contrast sensitivity at fixation, which are heavily impacted by corrupted neural retinal circuitry. We hypothesize that high-risk variants in the AMD susceptibility genes *ARMS2* and *CFH* increase the likelihood and rate of moving from one epoch to the next.

**Fig. 3 Fig3:**
[figure not shown]
Conceptual framework of visual impairment across retinal layers and time. Outer retinal neurovascular is at the bottom of the framework. Inner retina is at the top

In Fig. 3, we hypothesize that RMDA will be the earliest visual dysfunction in the aging to early AMD transition because of its dependence on the canonical retinoid re-supply route from ChC. As mentioned earlier, cones have an alternative source of retinoids. Thus, RMDA is more vulnerable to slowing than is cone-mediated dark adaptation, although we do not expect cones to be unaffected. We also hypothesize that as early AMD emerges (second epoch, Fig. 3) with rod photoreceptor outer segments shortening and degenerating, steady state scotopic (rod-mediated) light sensitivity will decrease. Steady state sensitivity refers to light sensitivity after the retina has ample time to adapt to the background luminance level of the target. Ultimately, as rods degenerate and die, retinal signal transmission and retinal circuitry (e.g., connections between rods and bipolar cells) will be corrupted further generating the formation of aberrant inner retinal connections [57–59] (third epoch, Fig. 3). This will result in deficits in mesopic central visual acuity and spatial contrast sensitivity at fixation, which are mediated by both rods and cones. ALSTAR2 is an opportunity to determine which types of rod dysfunction emerge before others. In addition, changes in cone-mediated vision can be directly compared to and contrasted with changes in rod-mediated vision in the same patients, an experimental paradigm that is seeing success in animal model studies [60].

In addition to examining structural and functional interrelationships in the aging to early AMD transition, ALSTAR2 will also reveal the timeline of several rod-mediated dysfunctions in aging and early AMD for insight into the neurophysiology of affected cells. The temporal relationship between RMDA delay, steady-state scotopic sensitivity loss, and mesopic central vision impairment in early AMD has not been established. We hypothesize that delayed RMDA will precede or possibly coincide with impaired scotopic sensitivity. Conversely, impaired scotopic sensitivity will not precede delayed RMDA. This hypothesis has preliminary support from cross-sectional studies but has not been examined longitudinally [6, 10, 61]. A second hypothesis is that delayed RMDA and scotopic sensitivity impairment will both precede deficits in mesopic visual acuity (mediated by both rods and cones) and central photopic contrast sensitivity (mediated by cones), measured at fixation. Cross-sectional studies have shown that eyes with early AMD can have modest impairments in mesopic visual acuity and contrast sensitivity, and these deficits can be more serious in intermediate AMD [62–67]. Further, impaired mesopic visual acuity and a low luminance deficit (disproportionate loss of mesopic acuity compared to photopic acuity) is associated with conversion to geographic atrophy, a form of advanced AMD [68].

## Methods/design

### Study design

The study was approved by the Institutional Review Board of the University of Alabama at Birmingham (UAB). All enrollees will provide written informed consent after the nature and purpose of the study are explained. Conduct of the study follows the tenets of the Declaration of Helsinki.

ALSTAR2 is a prospective cohort study with baseline measurements that are repeated at follow-up 3 years later. At baseline two groups of adults ≥60 years old are enrolled whose AMD status is determined by the AREDS 9-step classification system for color fundus photographs [69, 70]: (1) Those in normal macular health (AREDS grade 1) in both eyes, i.e., drusen equivalent diameter < 125 μm without increased pigmentation or depigmentation/ GA. (2) Those having early AMD (AREDS grade 2–4) in at least one eye, i.e. different combinations of drusen abundance and pigmentary change [69, 71]. The fellow eye can be any AREDS grade. We selected a 3-year follow-up period since changes in structural and functional characteristics in aging and early AMD are detectable over this period [16, 18, 19, 72]. We chose to use the AREDS 9-step grading system, despite the limitations of color fundus photography in revealing important details of AMD pathology, because it is validated and widely used [73, 74], and an equivalent system for OCT or other technology is yet to be devised. However, key pathology like SDD is visible in good color fundus photographs [75, 76] and are amenable to deep learning approaches [77] for detection and staging.

Exclusion criteria for those in normal macular health are (1) any eye condition or disease in either eye (other than early cataract) in the medical record that can impair vision including diabetic retinopathy, glaucoma, ocular hypertension, history of retinal diseases (e.g., retinal vein occlusion, retinal degenerations), optic neuritis, corneal disease, previous ocular trauma or surgery, refractive error ≥ 6 diopters; (2) neurological conditions that can impair vision or judgment including multiple sclerosis, Parkinson’s disease, stroke, Alzheimer’s disease, seizure disorders, brain tumor, traumatic brain injury; (3) psychiatric disorders that could impair the ability to follow directions, answer questions about health and functioning, or to provide informed consent; (4) diabetes; (5) any medical condition that causes significant frailty or is believed to be terminal. Exclusion criteria for the early AMD group are identical to those described above, except that it is acceptable for participants to have early AMD (AREDS 2–4) in one eye and be AREDS grade 1 or any stage of AMD in the fellow eye.

### Setting and protocol

ALSTAR2 is being conducted in the Clinical Research Unit of the Department of Ophthalmology and Visual Sciences at the University of Alabama at Birmingham, based at the Callahan Eye Hospital. Participants are recruited through the comprehensive eye care and retina clinics at the Callahan Eye Hospital. Participants from the first ALSTAR study [16, 71] are eligible to participate if they meet inclusion and exclusion criteria.

Table 2 lists assessments conducted in the protocol. All protocol elements are collected at baseline and then repeated at follow-up 3 years after baseline (with the exception of a blood sample for DNA extraction). Because of the length of the protocol, both baseline and follow-up consist of two separate visits within 1 week of each other, which together last approximately 4–6 h. Tropicamide 1% and phenylephrine hydrochloride 2.5% are used to dilate pupils (diameter of ≥6 mm) as needed for specific parts of the protocol.

**Table 2 Tab2:** Protocol assessments

Assessments	
**Visual Function Tests**	
Rod-mediated dark adaptation	
2-color dark-adapted microperimetry	
Light-adapted perimetry	
Photopic acuity	
Mesopic acuity	
Photopic contrast sensitivity	
Mesopic contrast sensitivity	
**Multi-Modal Retina Imaging**	
Color fundus photography	
Color fundus photography	
Near-infrared reflectance	
OCT-angiography	
Quantitative autofluorescence	
**Laboratory Assays**	
High density lipoprotein	
C-reactive protein	
DNA extraction and gene screening	
**Questionnaires**	
Demographics	
General health	
Medication use	
Alcohol use	
Smoking	
Low Luminance Questionnaire	
Vision in Low Luminance	
Montreal Cognitive Assessment	

Visual functional tests include tests of rod function, cone function and mixed rod and cone (mesopic) function. RMDA will be measured by the AdaptDx (MacuLogix, Harrisburg PA). Testing occurs in a dark, light-tight room, after dilation. RMDA will be measured at 5° (where rod loss is maximal in aging and AMD) and 12° (where rod density is maximal and rod loss is disproportionately less) [3, 4]. At 5° and 12° respectively, the rod-cone ratio is 8.5 at 5° and 23.2 at 12° in young adults and 6.3 and 18.3 in older adults (Table 1). RMDA will be tested in one eye only to minimize participant burden (i.e., in the eye with better acuity). The order of RMDA testing for the 5° and 12° targets will be counterbalanced across subjects. The procedure begins with a photo-bleach exposure to a 6° flash centered at the test target location on the superior vertical meridian on the retina (equivalent ~ 83% bleach; 0.25 ms duration, 58,000 scotopic cd/m^2^ s intensity [78]) while the participant focuses on the fixation light. Threshold measurement (3-down/1-up threshold strategy) for a 2° diameter, 500 nm circular target begins 15 s after the bleaching offset. The participant is instructed to maintain fixation and press a button when a flashing target first becomes visible within the bleached area. Log thresholds are expressed as sensitivity in decibel (dB) units as a function of time since bleach offset. Threshold measurement continues at 30-s intervals for 20 min, or until the rod-intercept time (RIT) can be estimated. RIT is the duration in minutes required for sensitivity to recover to a criterion value of 5.0 × 10^− 3^ scotopic cd/m^2^ [16, 79], located in the latter half of the second component of rod-mediated recovery [37, 80]. RIT is largely influenced by the rate of rhodopsin generation [37, 38, 81–85] and has good test-retest reproducibility (*r* = 0.95) [86]. RIT at the 5° and 12° test locations will also be compared within-subject to assess a parameter called “Rod Slope” [61].

Two-color dark-adapted microperimetry is a method that facilitates determining whether light sensitivity measurements are rod-mediated, cone-mediated, or have mixed mediation (both rods and cones) [87, 88]. Microperimetry will be tested in one eye only to minimize participant burden (the same eye tested for RMDA). After participants adapt to darkness for 30 min, the Scotopic MAIA (S-MAIA) microperimeter (CenterVue, Fremont CA) is used to measure light sensitivity in dB for a grid of 23 test targets presented in the macula (Fig. 4**)**. Targets are 0.43° in diameter (size Goldmann III); testing is carried out for both cyan (505 nm) and red (627 nm) targets after dilation. This “two-color” approach under dark adapted conditions is a well-established method in inherited retinopathy research [87, 88] and will verify whether sensitivity for the cyan target is indeed rod-mediated and not subject to cone intrusion. Thresholds not meeting the rod-mediated criterion are excluded from the characterization of scotopic sensitivity. Outcome measures will include both a global sensitivity across the macula and a regional or focal sensitivity, for specific eccentricities, meridians, and in correspondence to retinal structure.

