**Fig. 4 Fig4:**
[figure not shown]
Test locations for perimetry. The same 21 locations will be used for 3 test paradigms, the Humphrey Field Analyzer (for photopic sensitivity) and two-color dark-adapted microperimetry (cyan 505 nm, red 627 nm) using the MAIA-S. Perimetry will be tested in one eye only (the eye undergoing testing for RMDA tested at 5° and 12°). Targets are 0.43° in diameter (Goldmann III). Locations were chosen to sample closely near the fovea, where cell densities change rapidly with eccentricity and an effect of Bruch’s membrane lipidization is expected. In addition, targets in perifoveal and paramacular locations are included where rod density is high and subretinal drusenoid deposit is expected

Since cone-mediated sensitivity in the visual field is optimized for photopic light conditions, we will also assess sensitivity using a Humphrey Field Analyzer with a full-threshold procedure for a test grid identical to that of the S-MAIA as indicated above. The same eye as tested for dark adaptation and S-MAIA testing will be used.

Best-corrected visual acuity and spatial contrast sensitivity will be measured under both photopic (100 cd/m^2^) and mesopic (0.1 cd/m^2^) conditions for each eye separately. Visual acuity will be assessed using the Electronic Visual Acuity (EVA) tester [89] (JAEB Center, Tampa FL) and expressed as logarithm_10_ of the minimum angle of resolution. To achieve background mesopic luminance, participants will view the EVA through a 2.0 log unit neutral density filter. The “low luminance deficit (LLD)” for acuity [62], as it is called, is defined as the decrease in logMAR that occurs under mesopic conditions as compared to acuity under photopic conditions. Analogous to measuring LLD for acuity, we will assess the LLD for contrast sensitivity by measuring contrast sensitivity under both photopic and mesopic conditions as described above, using the Mars chart [90] (Mars Perceptrix, Chappaqua NY). The LLD for contrast sensitivity will be expressed as the difference in logarithm_10_ of sensitivity under photopic versus mesopic conditions. Both the EVA visual acuity tester and the Mars contrast sensitivity chart have high test-retest reproducibility [89, 91].

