With respect to multi-modal imaging, protocol elements consist of color fundus photography (CFP), SDOCT, near-infrared (NIR) reflectance, OCT angiography, and quantitative autofluorescence (qAF). OCT angiography is captured on the study eye only (eye tested for RMDA). Other modalities are captured on both eyes. CFP is used to document eligibility and AMD status. After pupil dilation, 3-field (30° diameter) stereo-fundus, digital photographs using a FF450^+^ camera (Carl Zeiss Meditec, Dublin CA) are taken. Photos will be evaluated by a trained grader with established inter-grader agreement (κ = 0.84) for presence and severity of AMD using the AREDS 9-step classification system [69]. The AREDS system grading is also converted to the more recently developed Beckman system [92]. Inter-grader agreement will be periodically monitored using a second grader with disagreements adjudicated by a fellowship-trained retina specialist ([name]). In addition, with the FF450+ camera, CFPs are captured at 2 additional magnifications (20° and 50°).

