### Sample size determination and analysis plan

Each study aim will estimate the association between two continuous variables, visual function and structure (e.g., RMDA as measured by rod-intercept time and RPE thickness). Sample size requirements are based upon the calculation of correlation coefficients. Table 3 presents sample sizes required to have at least 80% power (alpha = 0.05) to detect a range of correlation coefficients as statistically significant. Because no published study uses specifically our proposed structure and function measures and our patient population, we used the literature reporting structure-function correlations ranging from 0.1–0.6 in aging and AMD to guide sample size estimation [86, 108–111]. Studies finding correlations > 0.3 typically address later stages of AMD (intermediate AMD and GA). Because we focus on early disease, we anticipate weaker structure-function relationships, ~ *r* = 0.2. Using these considerations as guides to compute sample size, 193 AMD and 193 normal patients are required in order to achieve statistical power of 80%. Given the longitudinal study design, we bolster this sample size for losses to follow-up over 3 years and the inability of some patients to perform some vision tests. Based on the ALSTAR1 experience [16, 71], we increase sample size by ~ 20% to address anticipated loss to follow-up. Thus, we enroll 240 each of persons in normal macula health and those with early AMD. We will also be including study of 20 young adults ages 20 to 30 years old to serve as a reference group, against which the older adults can be compared. They will participate in the same baseline protocol as the older adults.

**Table 3 Tab3:** Sample Size Determination in ALSTAR2

Pearson correlation coefficient for alternative hypothesis	Sample size required
0.2	193
0.3	84
0.4	46

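### The early-AMD group is defined per person but RMDA, both perimetry tests and OCT angiography use the better-acuity eye, so some of its members may have these measures only in an eye without early AMD

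*Protocol article*

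**What the plan says.** Under Study design, the AMD group is "Those having early AMD (AREDS grade 2–4) in at least one eye", and "The fellow eye can be any AREDS grade". The exclusion criteria in the same section repeat this for the fellow eye: "it is acceptable for participants to have early AMD (AREDS 2–4) in one eye and be AREDS grade 1 or any stage of AMD". Group membership is therefore a property of the person.

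Under Setting and protocol, the tested eye is fixed by another rule: "RMDA will be tested in one eye only to minimize participant burden (i.e., in the eye with better acuity"). The other single-eye measures follow it:

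- Two-color dark-adapted microperimetry: "Microperimetry will be tested in one eye only to minimize participant burden (the same eye tested for RMDA").
- Humphrey perimetry: "The same eye as tested for dark adaptation and S-MAIA testing will be used".
- OCT angiography: "OCT angiography is captured on the study eye only (eye tested for RMDA").

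Photopic and mesopic acuity and contrast sensitivity are measured in each eye separately. The remaining imaging (color photographs, SDOCT, near-infrared reflectance, quantitative autofluorescence) covers both eyes.

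The section on sample size and analysis counts people: "193 AMD and 193 normal patients are required in order to achieve statistical power of 80"%, with 240 enrolled per group to allow for about 20% loss.

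**The concern.** The rule that makes someone an AMD participant and the rule that picks the eye to test are not connected. Take a participant with AREDS 2–4 in one eye and grade 1 in the other. If the grade 1 eye sees better, RMDA, both perimetry tests and OCT angiography are done in that eye, and the results sit under the early-AMD label. A fellow eye beyond grade 4 can be chosen in the same way if it has the better acuity, though this is less likely.

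RMDA is the main dependent variable, and OCT angiography images the choriocapillaris for the third aim. For such a participant neither is ever collected in the early-AMD eye. Analysis can relabel the tested eye by its own grade, but it cannot recover measurements that were not taken. What is at stake is how far results described as early AMD come from eyes with early AMD, and how many such eyes stand behind the power statement for that group.

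**Working it through.** **Which measures are affected**

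| Measure | Eye(s) | Tied to an AREDS 2–4 eye? |
|---|---|---|
| RMDA at 5° and 12° | better-acuity eye | no |
| Two-color microperimetry | RMDA eye | no |
| Humphrey perimetry | RMDA eye | no |
| OCT angiography | RMDA eye | no |
| Acuity and contrast sensitivity, photopic and mesopic | each eye | not affected |
| Color photographs, SDOCT, near-infrared, qAF | both eyes | not affected |

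**The plan's own figure.** Inputs: r = 0.2, 80% power, two-sided alpha 0.05. By Fisher's z, n = ((1.960 + 0.842) / atanh(0.2))² + 3, with atanh(0.2) = 0.2027, which gives 193.97. Adding the usual bias term r / (2(n − 1)) gives 193.0, the stated 193. For r = 0.3 and 0.4 the same formula gives 84.0 and 45.8, against the stated 84 and 46. Allowing for 20% loss, 193 / 0.80 = 241.25, or 242, close to the stated 240. The arithmetic is sound. It leaves no slack, since 240 × 0.80 = 192.

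**Sensitivity to the affected share.** Let f be the share of AMD-group study eyes outside grades 2–4. The article gives no value, so f is an assumption. To give it a scale: if acuity carried no information about grade, half of the participants with one early-AMD eye and one grade 1 eye would be tested in the grade 1 eye, so f = 10% corresponds to 20% of the group having that pattern.

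If an analysis is confined to early-AMD study eyes, n = N(1 − f) and power ≈ Φ(√(n − 3) × 0.2027 − 1.960).

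| f (assumed) | n from 193 evaluable | Power | n from 240 at baseline | Power |
|---|---|---|---|---|
| 0 | 193 | 80% | 240 | 88% |
| 10% | 174 | 76% | 216 | 84% |
| 20% | 154 | 70% | 192 | 80% |
| 30% | 135 | 64% | 168 | 74% |

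The baseline columns are an upper limit, because some participants will be unable to complete a test.

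Enrolment needed to keep 193 evaluable early-AMD study eyes is 193 / (0.80 × (1 − f)): 269, 302 and 345 for f = 10%, 20% and 30%, against 240 planned. If the study eye had to be AREDS 2–4, f would be 0 and the planned 240 would stand.

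**The case against.** The strongest reply is that each aim relates two continuous variables, and structure is available in whichever eye is tested. A grade 1 fellow eye of an affected person gives a valid same-eye pair and lies on the continuum from aging to early AMD that the study sets out to describe. No passage says such eyes are dropped, so the power loss arises only if an analysis is confined to AREDS 2–4 eyes. Mixed eyes might even widen the structural range. All of this stands, and it is why the table is a sensitivity range and not an estimate.

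It is also true that the sample size is stated in patients and never promises 193 AREDS 2–4 eyes, and that the analysis section specifies no AMD-versus-normal contrast. Two points remain. The sample size is set separately for each group, and the Background describes comparing aged normal eyes with early AMD, so the label is meant to carry information about eyes. The analysis section names AREDS progression as a candidate confounder or effect modifier, but not the study eye's baseline grade.

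A reader might infer that choosing the eye on photopic acuity tilts the scotopic-versus-photopic comparison towards the study's hypothesis. The article does not support that. Selection would narrow the spread of study-eye acuity, but acuity is taken in both eyes and analyzed for the better and the worse eye. Photopic function also includes Humphrey and contrast sensitivity, and any parallel narrowing of rod function is unknown. No bias has been shown.

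**Conclusion.** The mismatch is real and nothing in the article corrects it: following the plan exactly can put RMDA, perimetry and OCT angiography from an eye without early AMD under the early-AMD label. How often this happens cannot be derived from the article. It depends on how many participants have a grade 1 fellow eye and on how acuity relates to grade. When the fellow eye is more advanced, the better-acuity rule may well choose the early-AMD eye, so the grade 1 direction is the main one.

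The size is therefore conditional. For analyses confined to early-AMD study eyes, power at r = 0.2 would be about 76%, 70% and 64% from 193 evaluable at assumed shares of 10%, 20% and 30%, and up to 84%, 80% and 74% at baseline.

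Two stronger readings should be resisted. It is not the case that all function tests miss the early-AMD eye, since acuity and contrast sensitivity are done in each eye. Nor is the stated 80% power wrong for the analysis as written, which counts patients and can use every tested eye. The point is worth correcting because the missing measurements cannot be recovered later, but it does not invalidate the structure-function associations.

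**What to change.** 1. In the AMD group, define the study eye as an eye graded AREDS 2–4, with better acuity as the tie-break when both eyes qualify.
2. For anyone already tested under the present rule, use the study eye's own baseline AREDS grade, not the person-level label, in the models. Report how many AMD-group study eyes fall outside grades 2–4. The article does not say how many people have been tested so far.
3. State that the same eye is tested at year 3, whichever eye then has the better acuity.

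The cost is a short wording change. Color photographs are already used to grade eligibility, and one-eye testing with its burden rationale is kept. There are two modest drawbacks: some participants are tested in a slightly worse-seeing eye, and the eye-selection rule then differs somewhat between the AMD and normal groups, which should be acknowledged wherever the groups are compared.

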In AMD, the presence of extracellular deposits in the macula – soft drusen and subretinal drusen deposits (SDD, a.k.a reticular pseudodrusen) – increase AMD progression risk and compromise metabolic exchange between the ChC and outer retinal cells. Our hypothesis is that scotopic dysfunction will be accentuated where drusen and/or SDD are present, with SDD having a greater negative impact than drusen on scotopic function both cross-sectionally and prospectively.RPE cell bodies lose epithelioid morphology before anterior migration or apoptosis, as evidenced by variability and thickening of the RPE band in OCT and dimming of fundus autofluorescence signal from organelles believed to contain bis-retinoids. The thickness of photoreceptor- and RPE-attributable reflective bands will be assessed for context. Our hypothesis is that variability in RPE cell bodies is associated more strongly with scotopic dysfunction than photopic function both cross-sectionally and prospectively.The vascular density of the ChC (proportion of BrM covered) is a measure of direct metabolic exchange capacity between plasma and outer retinal cells in aging and early AMD. ChC vascular density declines in aging, under individual drusen, and in complete RPE and outer retinal atrophy (cRORA; geographic atrophy) [21]. Our hypothesis is that decreased ChC vascular density is more strongly associated with scotopic dysfunction than photopic function both cross-sectionally and prospectively.

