### Background in physiology and aging

The human retina is overall dominated by rod photoreceptors over cones (rod:cone ratio, 21:1). Because AMD’s debilitating vision loss affects central vision, we emphasize that the macula is also rod-dominated, despite the presence of the fovea, according to histologic studies using computer-assisted flat mounts to ensure accurate and unbiased counts [3, 30] and then validated in vivo with single-cell imaging [31]. “Macula” is variably defined, and Table 1 shows photoreceptor content in subfields of the Early Treatment of Diabetic Retinopathy Study (ETDRS) grading grid, widely used to assess AMD prevalence, incidence, and severity by color fundus photography. In this grid, rods outnumber cones 8.7:1 in younger adults and 6.8:1 in younger adults. The central 1 mm diameter subfield contains the cone-only foveola (0.375 mm in diameter) and a few rods around its rim, accounting for the non-zero rod: cone ratio in Table 1. In younger and older adults, respectively, mean rod density is 4.2-fold and 3.2-fold higher than cones in the inner ring (para- and perifovea), and 12.9-fold and 10.1-fold higher in the outer ring (perifovea) [32, 33]. These studies showed that in aging macula, rods die before cones, in a parafoveal ring directly surrounding the fovea, where loss is 30% up to age 92 (Fig. 1a-c). Further, histology also revealed that the last photoreceptors surviving in late AMD are cones [3, 4]. A monotonic trajectory of greater loss of rods than cones, beginning in aging, is a parsimonious explanation for these data. It is important to note that the highest densities of rods are outside the ETDRS grid in an elliptical ring at 2–5 mm eccentricity and extending into the nasal retina. The principal signal source for FAF imaging (Aim 2) is RPE lipofuscin, long-lasting inclusion bodies within these cells, and this tracks photoreceptor topography precisely, with highest intensities overlying the rod ring [36]. Thus, parafoveal rod loss in aging is spatially uncorrelated with highest levels of lipofuscin-attributable autofluorescence, as noted [3].

**Table 1 Tab1:** Photoreceptor density (cells/ mm^2^) in human macula [3, 30]

ETDRS subfields (inner to outer radius in mm and degrees of visual angle)	Mean cells/ mm^2^ in subfield		Ratio of Rods to Cones
	Cones/ mm^2^	Rods/ mm^2^	Rods : Cones
	Ages 27-37 years		
Center (0 - 0.5 mm; 0 - 1.7°)	57,001	20,013	0.35
Inner (0.5 - 1.5 mm; 1.7 - 5.2°)	18,774	78,252	4.17

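### Dropping microperimetry thresholds that are not rod-mediated makes exclusion depend on the outcome, which biases scotopic sensitivity towards health by an unknown amount

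*Protocol article*

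**What the plan says.** The rule is in the protocol article, Methods/design, Setting and protocol, in the paragraph on two-color dark-adapted microperimetry. Comparing cyan and red targets "will verify whether sensitivity for the cyan target is indeed rod-mediated and not subject to cone intrusion". Then: "Thresholds not meeting the rod-mediated criterion are excluded from the characterization of scotopic sensitivity". The outcomes follow directly: "Outcome measures will include both a global sensitivity across the macula and a regional or focal sensitivity", the latter to be matched to retinal structure. The rule as stated makes no exception by eccentricity and gives the excluded points no floor or censored value.

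Three other places bear on it:
- Conceptual framework for study design expects that, as early AMD emerges, "steady state scotopic (rod-mediated) light sensitivity will decrease".
- Background in physiology and aging reports that "the last photoreceptors surviving in late AMD are cones".
- The first aim, in Background, hypothesizes that "scotopic dysfunction will be accentuated where drusen and/or SDD are present".

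**The concern.** The two-color test asks which receptor sets the cyan threshold. Where rods normally set it, it passes to cones, or becomes mixed, once rod sensitivity has fallen to about cone sensitivity. On the article's own account, rods fail first, cones survive, and the loss is worst at deposits. At such locations, failing the criterion can therefore be a sign of the very loss that the outcome is meant to measure, and the rule deletes it. Exclusion then depends on the outcome and, through the Aim 1 hypothesis, on the exposure as well.

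Three things are at stake:
- Average scotopic sensitivity is overstated, most in the worst eyes.
- Focal structure-function slopes are attenuated.
- A location that is rod-mediated at baseline and cone-mediated 3 years later leaves the follow-up average and takes its decline with it.

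The planned mixed model does not cure this. Its usual likelihood analysis relies on missing values being explained by observed ones, whereas here the point is missing because its current rod value is low.

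**Working it through.** **The plan's own figure.** The article gives no figure for the exclusion. Its nearest number is the sample size for r = 0.2 (two-sided alpha 0.05, power 80%). Fisher's z gives n = ((1.960 + 0.842)/atanh(0.2))² + 3 = 193.97. The bias-corrected form gives 193, as in Table 3. So r = 0.2 is the plan's own anchor and is used in steps 2 and 3. Exclusion rates, SDs and floors below are assumptions.

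**1. Focal effect at a deposit.** Assume a location SD of σ = 4 dB, a deposit that lowers rod sensitivity by 4 dB, and a cone floor c lying 6 dB below the normal rod mean. With α = (c − μ)/σ, the fraction excluded is Φ(α), and the mean of what is kept is μ + σ·φ(α)/(1 − Φ(α)).
- Unaffected, μ = 0: α = −1.5; excluded 6.7%; kept mean = 4 × 0.1295/0.9332 = 0.56 dB.
- Affected, μ = −4: α = −0.5; excluded 30.9%; kept mean = −4 + 4 × 0.3521/0.6915 = −1.96 dB.
- Observed difference: 2.52 dB of a true 4 dB, a ratio of 0.63.
- Over floors of 4 to 10 dB below the mean and effects of 2 to 6 dB, 43% to 92% of the effect remains.

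**2. Location-level association, true r = 0.20.** Simulation with standardized structure and rod sensitivity, dropping the lowest fraction of rod sensitivities:

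| Excluded | Mean shift (SD) | Slope | r | r if kept at floor | Mean shift at floor (SD) |
|---|---|---|---|---|---|
| 5% | 0.11 | 0.16 | 0.18 | 0.199 | 0.02 |
| 10% | 0.20 | 0.15 | 0.17 | 0.197 | 0.05 |
| 20% | 0.35 | 0.12 | 0.155 | 0.193 | 0.11 |

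At 10% overall, the worst structural decile loses 17% of its locations and the best decile 5%.

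**3. Person-level global mean.** 21 locations, with between-person and within-person SDs assumed equal:

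| Excluded | Slope retained | r (0.203 with none excluded) | Slope retained if kept at floor |
|---|---|---|---|
| 5% | 87% | 0.197 | 95% |
| 10% | 79% | 0.195 | 90% |
| 20% | 66% | 0.192 | 80% |

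The slope shrinks but the correlation hardly moves. A floor reduces the slope bias without removing it.

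**4. Change over time.** Take 21 points at 20 dB at baseline. At follow-up, 4 have fallen to a non-rod-mediated cyan threshold of 8 dB. Keeping 8 dB as an upper bound, the mean rod sensitivity is at most (17 × 20 + 4 × 8)/21 = 17.7 dB. After exclusion it is 20.0 dB, and the decline of at least 2.3 dB vanishes.

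**5. Where failure need not mean disease.** The article puts the cone-only foveola at 0.375 mm in diameter. That is a radius of 0.1875 mm, or 0.66° at 3.5° per mm. Table 1 gives the central subfield, out to 1.7°, a rod-to-cone ratio of 0.35 in younger and 0.27 in older donors. The Fig. 4 legend says that sampling near the fovea is deliberately close. Some healthy points that do contain rods may therefore fail the criterion.

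**The case against.** The rule has a sound purpose. A cone-mediated threshold is not a measure of rod sensitivity, and keeping it at face value would also overstate rod function. That stands, and it is why the remedy is censoring and not simple retention.

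A reader might infer that every failure outside the rod-free foveola is evidence of rod loss. The documents do not support this. Step 5 shows a cone-dominated zone wider than the foveola, the article recognizes mixed mediation as a separate class, and the criterion itself is left to cited work.

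A reader might also take the 37% loss in step 1 as an estimate. It is not, since the article gives no SD, deposit effect, floor or exclusion rate. Exclusions may be few: one enrolled group has normal maculas in both eyes, the other has early AMD in at least one eye, and the tested eye is the one with better acuity. Classification from two noisy thresholds would also be looser than the sharp cut modeled here.

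Finally, a reader might infer that the central hypothesis or the study's power is undermined. The unifying hypothesis and the worked Aim 2A model use RMDA as the dependent variable, which this rule does not touch. The person-level correlation, the kind of quantity on which the study is sized, barely changes. Reading the location-level correlations in step 2 as power at n = 193 gives 0.71, 0.66 and 0.575 in place of 0.80, but that treats each person as one location and does not describe the planned clustered analysis.

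The direction of the bias survives all of this. Nothing else in the article treats the excluded points differently.

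**Conclusion.** The point holds for the microperimetry outcome. At locations that are normally rod-mediated, exclusion depends on the outcome. It biases scotopic sensitivity towards health, attenuates focal structure-function slopes (Aim 1 especially) and can hide 3-year decline. The direction follows from the article's own biology and appeared in every scenario tried. The size is unknown, and all percentages above rest on assumed inputs. RMDA outcomes are not affected. This should be fixed before analysis, but it does not threaten the study's main conclusion.

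**What to change.** 1. Fix in advance, by eccentricity, the near-foveal points that are normally cone-dominated or mixed, not only the rod-free foveola. The normal-macula group or the young reference group can be used to set them. Exclude these points for everyone and at both visits.
2. At all other points, keep a non-rod-mediated cyan threshold as an upper bound on rod sensitivity, that is, left-censored in a mixed model. Setting these points to a floor can serve as a sensitivity analysis.
3. Report the number of non-rod-mediated locations per eye and visit as a companion outcome.
4. Reconcile the size of the grid, which that count needs as its denominator. Setting and protocol has "a grid of 23 test targets presented in the macula", while the Fig. 4 legend says "The same 21 locations will be used for 3 test paradigms".

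The cost is a change of analysis wording and a censored-likelihood model. The two-color thresholds are already to be collected. The downside is a distributional assumption for the censored points, which the floor analysis helps to probe.
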